## Methods

### Participants

The study population consists of individuals with chronic pain. Inclusion criteria are as follows: (1) chronic nonmalignant pain defined as pain in one or more anatomical regions persisting for more than 3 months, present on most days of the week, and associated with significant emotional distress or functional disability, (2) a minimum age of 18 years, (3) sufficient knowledge of German, and (4) regular access to an internet-enabled device (computer or tablet). Exclusion criteria include acute suicidal ideation, uncorrected hearing impairments, significant language barriers, and current participation in psychotherapy. Current participation in structured psychotherapeutic treatment for chronic pain is an exclusion criterion to avoid overlap with the psychotherapeutic components of CHRONIC. Concurrent physiotherapy and routine medical care are allowed because the physiotherapeutic component of CHRONIC is intended as an adjunct to routine physical care but should be recorded and considered in sensitivity analyses.

### Study Design

This is an interventional, randomized controlled trial (RCT) with 3 parallel arms, including a nonblinded TAU group. The 2 experimental groups (EGpsych and EGcomp) complete 3 assessments: baseline prior to intervention start (T0), postintervention at week 12 (T1), and a 3-month postintervention follow-up, which represents the primary end point (6 mo after baseline, T2). In contrast, the TAU group follows an extended assessment schedule due to the 6-month waiting period: TAU participants complete a baseline measurement at study entry (T0), a second assessment following the 6-month waiting period and immediately before accessing the intervention (TAU-T1), a postintervention assessment after completing the 12-week program (TAU-T2), and a 3-month follow-up (TAU-T3). The 2 experimental groups receive access to the digital self-help program CHRONIC. Participants in the TAU group will receive access to the CHRONIC program with standardized computer-generated feedback (EGcomp version) after completing the 6-month waiting period. The 6-month waiting period for the TAU group was selected for 3 reasons. First, it reflects real-world access barriers in specialized pain services in Germany, where waiting times of 4 to 6 months are frequently reported for multidisciplinary pain treatment programs and specialist behavioral interventions, making this duration clinically realistic rather than arbitrary [3,23]. Second, extending the waiting period increases the likelihood of detecting natural symptom progression and pain chronification effects, allowing a meaningful comparison with the intervention arms and preventing artificially low variance caused by very short control periods. Third, choosing a 6-month window enables methodological alignment with the intervention design: since participants in the experimental arms undergo a 12-week treatment followed by a 3-month follow-up, the 6-month TAU period ensures comparable temporal exposure before receiving access to the program. The groups differ in the type of feedback received after each module: participants in the EGpsych receive individualized feedback written by the study team, whereas participants in the EGcomp receive standardized, template-based, computer-generated feedback. The study design is illustrated in Figure 1.

**Figure 1. F1:**
[figure not shown]
Study design.

### Ethical Considerations

Ethical approval was granted by the Ethics Committee of the Hannover Medical School (approval ID 11563_BO_S_2024), and the trial was prospectively registered in the German Clinical Trials Register (ID DRKS00036901) on May 19, 2025.

All participants were informed about the purpose and procedures of the study, the voluntary nature of participation, and their right to withdraw at any time without disadvantage. Informed consent was obtained from all participants prior to their participation in the study.

The authors confirm that all collected data were handled confidentially and processed in compliance with applicable data protection and privacy regulations. No personally identifiable information is disclosed in this manuscript.

### Sample Size

An a priori power analysis was conducted in G*Power (version 3.1.9.7; Erdfelder, Faul, and Buchner) to estimate the sample size required to detect a small-to-medium longitudinal intervention effect in a group comparison. Consistent with common planning approaches for repeated-measures trials, the calculation targeted the group × time interaction under conservative assumptions and serves as an approximation for the primary longitudinal analyses. We assumed an effect size of *f*=0.20, *α*=.025 and statistical power=.95. The correlation among repeated measures was set to *r*=0.50 and the nonsphericity correction to *ε*=0.75 to account for plausible deviations from perfect sphericity. Under these assumptions, G*Power yielded a minimum required sample size of 114. To account for dropout, a target sample size of 200 was prespecified. This inflation reflects the increased risk of dropout in the TAU control group due to the 6-month waiting period and the typical loss to follow-up in digital health trials. The larger sample ensures robustness against assumption violations and maintains adequate power.

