### Statistical Analysis

All statistical analyses will be conducted using the statistical software R (version 4.5.0; R Core Team). For the PP analysis, “full adherence” will be defined a priori. Participants must complete at least 9 out of the 12 intervention modules (≥75% completion rate) within the intended 12-week intervention period to be included in the PP dataset. Thresholds such as completing ≥75% of modules are commonly reported in digital intervention research to operationalize adherence criteria, although empirical justification varies across studies, and this threshold is considered consistent with existing eHealth adherence frameworks [28]. Participants who complete fewer than 9 modules or who finish all modules in an implausibly condensed time frame that violates the intended weekly structure will be excluded from the PP dataset. First, all primary and secondary outcomes as well as participant demographics and baseline characteristics will be analyzed descriptively (means, SDs, and frequencies), both for the total sample and stratified by the study group (EGpsych, EGcomp, and TAU). To examine intervention effects, mixed models for repeated measures will be used as the primary analytic approach. The mixed models for repeated measures allow the inclusion of all available outcome data and accommodate unequal assessment schedules between groups due to the 6-month waiting period in the TAU condition. The primary randomized comparison will focus on the matched assessment approximately 6 months after baseline, corresponding to the 3-month follow-up in the experimental groups (T2) and the end of the waiting period in the TAU group (TAU-T1). For each primary and secondary outcome, models will include fixed effects for group (EGpsych vs EGcomp vs TAU), time (baseline vs matched 6-mo assessment), and the group × time interaction. A participant-specific random intercept will be included to account for within-person correlation. The group × time interaction will be used to test differential change between conditions. Holm-corrected post hoc contrasts will be applied for pairwise comparisons where applicable. If model assumptions are violated, appropriate robust methods will be considered. Outcome data collected in the TAU group after participants have received access to CHRONIC (eg, TAU-T2 and TAU-T3) will not be included in the primary randomized comparison because TAU no longer represents a control condition at that stage. Post-waitlist TAU data will instead be analyzed separately and within-group (exploratory) to describe changes following delayed program access. Exploratory analyses within each study arm will be reported descriptively. However, comparisons across nonmatched time intervals will not be interpreted as randomized sensitivity analyses. When a significant main or interaction effect is detected, Holm-corrected post hoc tests will be applied to determine the specific time points and group differences, while controlling for the family-wise error rate.

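### The N=114 calculation has 95% power only for a difference in change of about 0.85 to 0.90 SD, so the stated power for a small-to-medium effect is not supported

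*Protocol article*

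**What the plan says.** The Sample Size section of the protocol article describes an a priori G*Power calculation whose purpose was "to estimate the sample size required to detect a small-to-medium longitudinal intervention effect in a group comparison". It says that "the calculation targeted the group × time interaction under conservative assumptions". The inputs are:

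- "We assumed an effect size of *f*=0.20, *α*=.025 and statistical power=.95"
- "The correlation among repeated measures was set to *r*=0.50"
- "the nonsphericity correction to *ε*=0.75 to account for plausible deviations from perfect sphericity"

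The result is that "G*Power yielded a minimum required sample size of 114". The target was then raised to 200 for dropout, without a stated rate, and the section ends: "The larger sample ensures robustness against assumption violations and maintains adequate power".

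The section does not say how many groups and measurements were entered, which effect-size option was used, or what f=0.20 means in SD or scale units.

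The Statistical Analysis section fixes the primary model: three groups, "time (baseline vs matched 6-mo assessment", and the group × time interaction. Time therefore has two levels.

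**The concern.** The value of f for a within-between interaction cannot be read on its own. The size of effect it stands for depends on the software option and on the number of time points. A label borrowed from the general convention for f can describe a much larger difference in change than a reader would picture.

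If so, the protocol claims a power that its inputs do not give for an effect of the size named. Someone reading a null result would take the trial to have had a 95% chance of finding a small-to-medium benefit and might count the result as strong evidence against CHRONIC. The calculation also has to describe the planned primary model, which has two time points and no use for a sphericity correction.

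**Working it through.** **1. Inputs.** From Sample Size: f=0.20, alpha=.025, power=.95, r=0.50, ε=0.75, N=114, target 200. From Study Design: three arms, and three assessments in the experimental arms. From Statistical Analysis: two time points in the primary model. Equal allocation is my assumption, because the article states no ratio.

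**2. Reproducing N=114.** For the interaction under the G*Power default option, with k groups and m measurements:

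- λ = f²·N·m·ε/(1−r)
- df1 = (k−1)(m−1)ε
- df2 = (N−k)(m−1)ε

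With k=3, m=3 and N=114: λ = 0.04×114×3×0.75/0.50 = 20.52, df1 = 3, df2 = 166.5, power 0.954. At N=111 power is 0.948, so 114 is the first multiple of three that passes. The other settings tried do not give 114:

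| Groups × times | ε | N |
|---|---|---|
| 3×2 | 0.75 | 144 |
| 3×2 | 1 | 117 |
| 2×2 | 0.75 | 122 |
| 2×3 | 0.75 | 96 |
| 3×4 | 0.75 | 96 |

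Under the alternative (SPSS-style) option, 3×3 gives 333 and 3×2 gives 561. The default option is therefore inferred from the protocol's own result.

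**3. What f=0.20 means there.** In that option f is the SD of the interaction cell effects divided by the raw within-cell SD, and r enters separately. Suppose both CHRONIC arms change by d raw SD more than TAU. The centred group effects are d/3, d/3 and −2d/3, with mean square (2/9)d².

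- *Two time points.* Centred time effects are −½ and ½, mean square ¼. So f² = ¼×(2/9)d², f = 0.236d, and d = 0.20/0.236 = 0.85.
- *Three time points, effect present at both later visits.* Centred time effects are −2/3, 1/3 and 1/3, mean square 2/9. So f² = (2/9)²d², f = 0.222d, and d = 0.20/0.222 = 0.90.

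With r=0.50 the SD of change is √[2(1−0.5)] = 1.00 raw SD, so these are also SDs of change. A simulation of the two-time-point model at N=114 gave power 0.948 at 0.85 SD and 0.31 at 0.40 SD.

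**4. Power of the planned primary test for smaller effects.** The 3×2 interaction equals a one-way test on change scores, with λ = N(2/9)d²/[2(1−r)] and 2 and N−3 degrees of freedom. For d=0.5, N=114, r=0.50: λ = 114×0.2222×0.25/1 = 6.33, power 48%. At alpha=.025 and r=0.50:

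| Evaluable N | Loss from 200 | d=0.4 | d=0.5 | d=0.85 |
|---|---|---|---|---|
| 114 | 43% | 30% | 48% | 95% |
| 140 | 30% | 38% | 59% | 98% |
| 160 | 20% | 44% | 66% | 99% |
| 200 | 0% | 55% | 78% | >99% |

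The difference detectable with 95% power is 0.85 SD at 114 and 0.64 SD at 200.

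**5. Sensitivity to r** (d in raw SD, same formula). At d=0.5 and N=160, power is 66% at r=0.5, 77% at r=0.6 and 89% at r=0.7. At d=0.5 with all 200 evaluable it is 78%, 87% and 95%.

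**The case against.** - **The label follows convention.** f=0.20 does lie between the usual small and medium marks for f, and N=114 is a correct output for the inputs. Both points stand. A reader might infer an arithmetic error in N, and there is none. The fault is that the label does not carry over to a difference in change.
- **The intended effect is not known.** A reader might take f=0.20 as a between-group effect on change scores, which is 0.20/√(2/9) = 0.42 SD, and conclude that true power is 34%. The section never gives that meaning. The figure also belongs to 114 evaluable participants at r=0.50; for the same effect it is 43% at 140, 49% at 160 and 61% at 200. It is one point in a range and not a property of the trial.
- **The trial enrols 200, not 114.** Having only 114 evaluable would mean a 43% loss, and the plan analyses all randomized participants with multiple imputation. A reader might infer that a medium effect would more likely than not be missed. At 0.5 SD that holds only near N=114 (48%); from 140 upward power exceeds one half.
- **The medium effect in the Background is limited support.** It concerns pain-related functioning and pain acceptance in another online ACT program. It does not cover pain intensity or quality of life, and it is not given as a difference in change in raw SD.
- **The calculation is called an approximation.** For the number of time points this is a fair defence: 117 against 114 is immaterial beside 200. It does not cover a detectable effect of 0.85 to 0.90 SD described as small to medium.
- **The SD conversion rests on assumptions.** The 0.85 SD figure needs equal allocation; with half of the participants in TAU it would be 0.80. In a three-time-point layout, a contrived pattern with a different time course in each arm can reach about 0.73. Neither comes near 0.4 to 0.5.

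**Conclusion.** The point holds. The inputs that give N=114 provide 95% power for about a 0.90 SD difference in change in the 3×3 calculation, or about 0.85 SD in the planned two-time-point model. That is a large effect, and the wording of the section leads a reader to expect a much smaller one.

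If small-to-medium means 0.4 to 0.5 SD in change, power at r=0.50 runs from 30-48% at 114 evaluable to 55-78% at 200. At the protocol's own r, even complete follow-up gives 95% power only from about 0.64 SD, so the closing claim of adequate power is unsupported for the effect named. A higher correlation narrows the gap. It closes at 0.5 SD only with r near 0.7 and no dropout.

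These figures rest on equal allocation, a common benefit in both CHRONIC arms, and my SD reading of the label. They do not show that 200 is the wrong sample size.

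**What to change.** Keep N=200 and rewrite the Sample Size paragraph:

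1. State the target effect as a standardized difference in 6-month change between CHRONIC and TAU.
2. Base the calculation on the 3-group × 2-time primary model and drop ε, which has no role with two time points.
3. State the allocation ratio and the dropout assumed.
4. Report power at about d=0.4, 0.5 and 0.85 for 114 to 200 evaluable participants, over a range of r such as 0.5 to 0.7.
5. Delete the small-to-medium label and the adequate-power sentence, or qualify them by saying that N=114 targets about 0.85 SD in change.

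The cost is one reworded paragraph and a less favourable stated power. No patients are added, and neither the design nor the analysis changes.

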### Procedure and Recruitment

Participants are recruited via digital platforms (eg, online forums and patient advocacy groups) as well as through direct cooperation with health care providers (eg, pain clinics, physiotherapy practices, and orthopedic clinics). Interested individuals are provided with detailed study information through an online portal, including an introductory video explaining the intervention. Support is available via a dedicated project email address. Upon registration and consent, participants undergo an onboarding process to assess eligibility and complete the baseline measurement (T0). All assessments are administered digitally through the intervention platform. Participants are pseudonymized using computer-generated codes. The link between codes and participant information is stored separately in an encrypted file accessible only to the study team. This file allows reidentification solely for data deletion upon participant request, ensuring compliance with data protection standards.

### CHRONIC Web Application

CHRONIC is a digital, web-based intervention grounded in a combination of ACT [11] and CBT. The program is further enhanced by the integration of mindfulness-based strategies and physiotherapeutic components, drawing on practical experience in the treatment of patients with chronic pain. Over the course of a 12-week self-help program, users are guided to develop a deeper understanding of their pain condition and of themselves, foster pain acceptance, improve emotional regulation and stress management, and define concrete personal goals for future behavior and life planning. Core components include strengthening personal responsibility and building internal and external resources. From a physiotherapeutic perspective, the intervention promotes physical functionality through posture training, a full-body exercise program (adaptable in intensity), and practical knowledge for maintaining safe gait and stance to support current and future mobility. Mindfulness exercises are interspersed between modules to sharpen external awareness and enhance attentional control. Table 1 provides an overview of the program modules and their respective contents. To ensure clinical relevance and theoretical coherence, the content and sequencing of the CHRONIC modules were derived from a combination of empirically supported treatment principles and clinical experience in treating individuals with chronic pain. The psychotherapeutic modules are grounded in core components of ACT, whose effectiveness in digital self-help formats for chronic pain has been demonstrated, for example, in the evaluated digital health application “HelloBetter Chronischer Schmerz.” Complementing this, the physiotherapeutic components were selected based on real-world clinical demands frequently observed in outpatient settings: physical deconditioning, insecure movement patterns, and fear of movement. To address these, CHRONIC includes functional exercises (adaptable in intensity), postural guidance, and educational input on safe movement execution, aiming to promote mobility confidence and bodily self-efficacy. Mindfulness-based exercises interwoven throughout the program serve to enhance interoceptive and attentional awareness, supporting both psychological flexibility and functional engagement. Overall, the selection of modules reflects a biopsychosocial rationale: each session builds on previous content and targets a distinct yet interrelated aspect of pain coping. This structure allows participants to develop adaptive cognitive, emotional, behavioral, and physical strategies in a coherent, cumulative manner over the course of the 12-week program.

**Table 1. T1:** Overview of the CHRONIC program modules.

Module	Description of content
1. Pain and now?	Psychoeducation on the topic of chronic pain, including an overview of the program and introduction of the assigned therapist.
2. Becoming fully awake	Participants are introduced to the concept of mindfulness, which involves observing the present moment without judgment. This session focuses on cultivating the ability to consciously direct attention to the here and now.
3. Understanding pain	Accepting the current state of one’s condition is often perceived as counterintuitive or even unimaginable. This session explores why acceptance can nonetheless lead to long-term improvement in symptoms and overall functioning.
4. Do you feel that too?	Emotions are a constant part of human experience. While some are perceived as pleasant and others as distressing, this session addresses strategies for managing the full range of emotional experiences in an adaptive manner.
5. Don’t stress me out	Stress is a common experience; yet in the context of chronic pain, it can become particularly overwhelming. This session provides techniques for more effective stress regulation.
6. Bird’s-eye view	Defusion refers to a mental state in which thoughts and emotions are observed without becoming entangled in them. Participants learn how to develop a more distanced and less reactive stance toward internal experiences.
7. What matters to me	Personal beliefs significantly influence both cognition and behavior. Conversely, engaging in actions aligned with one’s core values can help reinforce a meaningful and coherent sense of self. This session explores this bidirectional relationship.
8. Commitment of the self	Living a meaningful life requires ongoing commitment. This session introduces the concept of value-based goal setting and encourages participants to formulate personal commitments that support long-term well-being.
9. In the here and now	People often dwell on the past or worry about the future. This session highlights the benefits of present-focused awareness and offers practical guidance for anchoring attention in the here and now.
10. The creature of habit	Changing entrenched behavior patterns is inherently difficult. In this session, participants reflect on habitual behaviors and explore strategies for initiating and maintaining adaptive behavioral change.
11. Reinforcement from within	This session centers on personal resources—both internal and external—that contribute to resilience and psychological flexibility. Participants are encouraged to identify, sustain, and further develop these resources.
12. …and last but not least	The final session acknowledges the participants’ engagement throughout the program and emphasizes the importance of continuing to invest in one’s health and well-being beyond the structured intervention.
Physiotherapy module 1	Introduction to physiotherapeutic principles: education on ergonomic posture, everyday movement patterns, and alignment correction to reduce pain load during daily activities.
Physiotherapy module 2	Guided whole-body exercise routine designed to improve strength, stability, and mobility; intensity levels adjustable by participants based on functional capacity and pain level.
Physiotherapy module 3	Movement retraining for walking and standing; focus on biomechanical efficiency and safety.

The program is structured so that participants complete one psychotherapeutic unit per week, followed directly by either a physiotherapy or mindfulness-based unit. Each weekly session is designed to take approximately 50 minutes, with the intention that users apply the learned content between sessions in their everyday lives. Users can revisit all materials as often as they wish during the 12-week access period. The psychotherapeutic sessions are delivered via video recordings of a licensed psychological psychotherapist, who explains the core content of each session and poses interactive questions during the modules. Videos pause automatically when user input is required, and corresponding exercises are displayed on screen. Upon completion of an exercise, marked by the user, the video continues. At the end of each session, users can download their completed exercises or obtain blank worksheets for printing and future reuse.

Modules are time-locked to ensure standardized intervention exposure because the intervention is designed to run over a fixed 12-week period. Each new module becomes available exactly 7 days after the previous module has been released. Participants cannot access future modules ahead of schedule, and early progression or skipping forward is technically prevented. The program cannot be paused. All participants have a fixed consecutive 12-week access period, after which access to the intervention ends automatically. If participants choose not to complete a module in the week it becomes available, the next module is still released on schedule 7 days later. This allows participants to complete multiple outstanding modules in a shorter interval later on, reducing the time gaps between sessions while still operating within the fixed 12-week intervention window. All completion times and access patterns are recorded through backend timestamps and will be evaluated in adherence. To support structured engagement and continuity in self-monitoring, brief intersession assessments are implemented within the platform workflow. Before participants can begin the next module, they are required to complete a short check-in assessment referring to the preceding week, based on subscales derived from the West Haven-Yale Multidimensional Pain Inventory (WHYMPI; part 1 “Pain experience statements” and part 3 “Patient activity”). These assessments are integrated directly into the platform interface and are automatically presented at the start of each new session. The check-ins occur once per week, require approximately 2 minutes to complete, and refer to the participant’s experiences during the previous 7 days. Modules cannot be accessed until the corresponding check-in is completed, ensuring a consistent measurement structure across participants. There is no fixed time of day for completion since the brief assessment appears immediately when the new module is opened and remains available until submitted. These data are visualized in real time on the user’s personal dashboard as a line graph based on the summed scores to support self-monitoring. After each module, participants in the experimental groups receive motivational feedback—either individualized or computer-generated, depending on group assignment—delivered via the app and email shortly after session completion. Feedback is only triggered following the completion of a module. The feedback procedure differs between the 2 intervention conditions. In the EGpsych arm, feedback is written individually by psychologists from the study team. All potential feedback providers hold a university degree in psychology and have additional clinical experience in working with individuals with chronic pain. Feedback integrates participant-specific information derived from the weekly self-assessments. Messages are delivered asynchronously in written text format via the platform interface. In contrast, participants in the EGcomp arm receive standardized feedback messages prewritten by psychologists from the study team based on a fixed template system. These messages include the same structural components as in EGpsych (completion acknowledgment, motivational reinforcement, psychoeducational element, and goal reminder), but they do not integrate individual self-assessment data or module-specific personal content. The feedback is identical across all EGcomp participants and does not vary based on adherence patterns or timing. This standardized structure ensures consistency in length, tone, and delivery frequency across participants while maintaining methodological separation from tailored guidance. In both intervention arms, feedback messages are delivered asynchronously via the platform and email notification within 24 hours following module completion, and participants cannot respond to feedback in either condition. The feedback texts contain approximately 100 to 150 words per module. If participants complete multiple modules within a single day (catch-up use), EGpsych feedback is not provided separately for each module. Instead, one feedback message is provided referencing the last completed module and comparing the most recent assessment with the prior assessment, thereby reflecting the latest available change pattern rather than generating multiple module-specific feedback messages. Such accelerated completion patterns and potential overlaps in assessment windows are captured via timestamps and will be considered in adherence metrics and per-protocol (PP) definitions.
